## Discussion

### Principal Findings

In this report, we describe the rationale, design, and initial implementation outcomes of a 3-arm pragmatic trial that assessed the feasibility and preliminary effectiveness of an eCDSS to improve CKD management in primary care compared with usual care. This study builds on previous pragmatic trials focused on EHR-based interventions to improve CKD management [28,29,51,52] and supports the feasibility of using EHRs to identify study participants, intervene in early CKD management, and measure study outcomes. Given its design as a pragmatic trial (per Pragmatic Explanatory Continuum Indicator Summary, or PRECIS, criteria [53]), we found high rates of participation by providers and low opt-out rates by patients. We also found high rates of eCDSS use by providers.

This study has many innovative components. We utilized a 3-armed trial design, which included a usual care group as well as a group with pharmacist-patient engagement after the provider-facing electronic intervention. In addition, our clinical eCDSS was mostly automated and individualized to patients based on laboratory results, rather than a generic CDSS for all participants. We also implemented the recommended triple-marker risk stratification approach to better characterize participants’ risk for CKD progression. Our participants included non-English speakers, who have been excluded from many other trials. This trial also included multiple types of outcomes allowing for a deeper understanding of the intervention’s impact on care processes. Reviews of eCDSS have found that few studies assess unintended consequences or adverse effects of a CDSS, which can be widespread as CDSS interventions often automate multiple actions [54,55]. This trial integrated safety measures and their tracking by a nephrologist allowing not only for measurement of safety but also the ability to ensure that any new concerning clinical findings found owing to the trial would be addressed. As previously recommended, it is important to first pilot interventions before widespread implementation to ensure there are no adverse effects in a small population where safety can be more easily assessed [56].

One of the greatest challenges of this trial was its dependence on data analysts experienced at working with the EHR to program and implement the intervention as well as extract outcomes data. The study team devoted substantial time to troubleshoot unanticipated problems with the eCDSS programming and capture of outcomes. Every update or change to the EHR processes had the potential to disrupt the trial implementation. The team regularly validated the eCDSS and data capture through manual chart reviews. The inaccuracies of EHR data extraction are well-documented [57]. Despite the presence of an explicit trial infrastructure in our EHR, implementation of the intervention and data collection was far from seamless. Studies that rely on the EHR to deliver interventions and collect outcomes must ensure adequate time and resources for a multidisciplinary team to validate the intervention and review data inaccuracies in an ongoing manner for all EHR-based trials.

### Comparison With Previous Work

In this trial, we found much higher reach and adoption of eCDSS by PCPs than previous studies where adoption rates were frequently <50% [55,58]. We believe there are multiple explanations. Few electronic alerts are currently used in this practice, so providers have not yet experienced fatigue associated with the growing presence of alerts [59]. Moreover, the eCDSS was designed by a multidisciplinary team, facilitating buy-in from all stakeholders and ensuring all perspectives were considered in determining how the eCDSS would impact workflow. Finally, study staff (including a lead investigator who works within the primary care practice) served as on-the-ground champions and made significant efforts to educate, remind, and incentivize PCPs.

We experienced many of the same challenges as other pragmatic trials during implementation of this EHR-dependent intervention. There was a period of time between provider recruitment, randomization, participants being contacted to opt out, and the study start date; as a result, 18 patients passed away before randomization and 2 additional patients passed away before the start of the study. Importantly, nearly half of the participants in the intervention arms never completed the triple-marker screen and therefore never had the opportunity to receive the eCDSS interventions. Another one-fifth of participants who completed the triple-marker screen did not have a PCP visit after the triple-marker screening and also did not receive the eCDSS. These barriers, common in many eCDSS trials, prevented the intervention group from receiving the desired intervention.

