**Conclusions:**

Successful integration of an eCDSS into primary care workflows and high eCDSS utilization rates at eligible visits suggest this tailored electronic approach is feasible and has the potential to improve guideline-concordant CKD care.

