#### Completion of Triple Marker

Of the 336 patient participants in the intervention arms, 178 (53.0%) completed the triple-marker screening.

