#### PCP Visits

Of the 178 patient participants who completed a triple-marker screen, 138 (77.5%) had a PCP visit during the 12-month intervention period. This was 41.1% (138/336) of all intervention participants.

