#### PCP BPA Use

Of the 138 participants with a PCP visit, the BPA was opened for 102 participants (73.9%). This was 30.3% (102/336) of all intervention participants.

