### Limitations

As a pilot study, this study was limited by its inclusion of patients and providers from a single institution. Therefore, both the intervention and strategies to encourage intervention uptake were adapted to meet the needs of this single institution that uses Epic Systems’ EHR. However, we have found that the patient population in this clinic is similar to others [60], and Epic is a widely used EHR in multiple health systems. As a pragmatic trial, our sample size was smaller than initially anticipated and will thus ultimately impact our power to detect changes in our primary outcome. The short follow-up period for this pilot study will also limit our ability to assess some clinical outcomes. However, we were still able to use this pilot study to determine the feasibility of this intervention.

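### The claim of higher reach than earlier studies has no support, and the abstract's feasibility conclusion omits the all-patient use rates

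*Protocol article*

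**What the plan says.** In the Discussion (Comparison With Previous Work) the article states that "we found much higher reach and adoption of eCDSS by PCPs than previous studies where adoption rates were frequently <50" per cent. The abstract's Conclusions cite successful workflow integration and say that "high eCDSS utilization rates at eligible visits suggest this tailored electronic approach is feasible and has the potential to improve guideline-concordant CKD care". The Limitations section adds: "However, we were still able to use this pilot study to determine the feasibility of this intervention".

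The Results give the steps behind these statements. On laboratory testing: "Of the 336 patient participants in the intervention arms, 178 (53.0%) completed the triple-marker screening". On a PCP visit after the labs: "This was 41.1% (138/336) of all intervention participants". On opening the best practice advisory (BPA): "This was 30.3% (102/336) of all intervention participants". SmartSet Use then reports orders or education signed for 83 of the 102 patients whose advisory was opened (81.4%).

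Textbox 1 lists, under Reach, the recruitment rate, completion of the triple-marker labs, a PCP visit after them, and availability of the advisory. Its first Adoption outcome is signing the SmartSet among patients for whom the advisory was available.

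**The concern.** There are three linked problems.

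1. **The reach comparison.** The sentence claims superiority on both reach and adoption, but the only benchmark offered is an adoption rate. The trial's own lab and visit figures do not look like high reach. The paragraph that follows says that nearly half the intervention patients never completed the labs, that about a fifth of completers had no later visit, and that such barriers are common in trials of this kind.
2. **The denominator of the feasibility conclusion.** The only use rate behind the abstract's conclusion is conditional on an eligible visit. The 198 intervention patients without such a visit (336 − 138) cannot affect it.
3. **The Adoption denominator.** The outcome was planned over patients with the advisory available and is reported over patients whose advisory was opened.

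Feasibility is a stated aim (Trial Aims), and the closing Conclusions offer the results as a guide for later trials. Someone who takes uptake from the conclusion would carry forward roughly three quarters, when the tool was opened for under a third of the allocated patients.

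**Working it through.** **Inputs**, all from the Results: 336 intervention patients (165 + 171), 178 with labs complete, 138 with a later PCP visit, 102 with the advisory opened, 83 with orders or education signed.

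**Reproducing the printed figures.** 178/336 = 53.0%; 138/178 = 77.5%; 138/336 = 41.1%; 102/138 = 73.9%; 83/102 = 81.4%. All agree. 102/336 = 30.36%, which rounds to 30.4% and is printed as 30.3%, a trivial slip.

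**All allocated intervention patients as denominator** (Wilson 95% intervals). The last column allows for clustering by PCP with design effect 1 + (m − 1) × ICC. Here m = 336/53 = 6.34. The 53 intervention PCPs are inferred from the video-viewing percentages (18/25 = 72.0%, 19/28 = 67.9%, 37/53 = 69.8%). The ICC for these outcomes is not given and is an assumption, varied from 0.025 (design effect 1.133) to 0.20 (2.068).

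| Step | Count | Rate | 95% CI, unclustered | 95% CI, ICC 0.20 |
|---|---|---|---|---|
| Eligible PCP visit | 138/336 | 41.1% | 35.9–46.4 | 33.8–48.8 |
| Advisory opened | 102/336 | 30.4% | 25.7–35.5 | 23.8–37.8 |
| Something signed | 83/336 | 24.7% | 20.4–29.6 | 18.7–31.9 |

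So 58.9% had no eligible visit, 69.6% never had the advisory opened and 75.3% had nothing signed.

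**Adoption on its planned denominator.** The advisory was programmed to trigger at the first PCP visit after all three results were available, so I take the 138 patients with an eligible visit as those for whom it was available. Then 83/138 = 60.1% (unclustered 95% CI 51.8–67.9), against 81.4% reported. The 83/102 figure is closer to the first outcome under Implementation in Textbox 1, which is orders signed or education given after opening.

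**Why the denominator matters for planning (illustration only).** Suppose benefit arises only where the advisory was opened. For a between-arm difference of 1.27 mmHg, the article's design figure, the effect among opened patients would have to be 1.27/0.739 = 1.72 mmHg at the conditional rate, but 1.27/0.3036 = 4.18 mmHg at the all-patient rate.

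**The case against.** Most of the material is disclosed. The abstract prints the numerators and denominators of every step, the Results print 41.1% and 30.3%, and the Discussion describes the losses in the paragraph after the disputed sentence. The abstract states its condition (eligible visits) and hedges with suggestion and potential. Primary analyses follow intention to treat, so unreached patients are not dropped from the comparison of arms. All of this stands, and it limits the point to how conclusions are worded and on which denominator.

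The adoption half of the sentence is also defensible. Given an eligible visit, opening (73.9%) and signing (60.1%) both exceed 50%. The denominators of the earlier studies are not in the article, so it cannot be said that this trial did worse than they did, even though the all-patient limits above lie below 50%.

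A reader might infer that feasibility was judged only on patients who reached an eligible visit. The article does not support that: it also cites agreement by 81/81 PCPs, inclusion of 524/582 patients (90.0%) and low opt-out, and recruitment is itself a listed Reach outcome. A reader might also infer a decision rule that would declare success under no effect. The article contains no progression threshold or if-then rule, so no error probability can be attached to the conclusion.

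What the objection does not answer is the word *reach*. No comparator reach rate is given, and disclosure elsewhere does not supply one.

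**Conclusion.** The concern holds in a limited form. The claim of superior reach is unsupported and sits badly with the article's own 53.0% and 41.1%. The abstract's feasibility conclusion rests on a conditional use rate of 73.9% and leaves out that, of all 336 allocated intervention patients, the advisory was opened for 30.4% and something was signed for 24.7%. Adoption is reported at 81.4% where the planned definition gives about 60.1%.

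The point estimates need no assumption except the last, which equates an eligible visit with an available advisory. The clustered intervals rest on 53 inferred PCPs and an assumed ICC range; no point above depends on them.

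This is a defect of wording and denominator, not concealment, and it does not touch the design or the intention-to-treat comparison. Nor does the hedged phrase about potential to improve care amount to a claim of effect. No care outcome is compared between arms in this article, and the article says that it reports only the Reach outcomes and the first Adoption outcome.

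**What to change.** - **Comparison With Previous Work:** delete *reach* from the comparison and state the adoption claim as conditional on an eligible visit.
- **Abstract Conclusions and Limitations:** state feasibility as high PCP acceptance at eligible visits with limited patient reach. Give 41.1% (eligible visit), 30.4% (opened) and 24.7% (signed) of all 336 intervention patients beside 73.9%. Keep recruitment of PCPs and patients as supporting evidence.
- **SmartSet Use:** report Adoption on its planned denominator (83/138 = 60.1%, if the 138 are confirmed as those with the advisory available), and label 81.4% as signing after opening.
- **PCP BPA Use:** correct 30.3% to 30.4%.
- The phrase on potential to improve care may stay, with a note that no between-arm care outcome is yet reported.

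The cost is a few sentences based on counts already published. The stated feasibility becomes less favourable.

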### Limitations

As a pilot study, this study was limited by its inclusion of patients and providers from a single institution. Therefore, both the intervention and strategies to encourage intervention uptake were adapted to meet the needs of this single institution that uses Epic Systems’ EHR. However, we have found that the patient population in this clinic is similar to others [60], and Epic is a widely used EHR in multiple health systems. As a pragmatic trial, our sample size was smaller than initially anticipated and will thus ultimately impact our power to detect changes in our primary outcome. The short follow-up period for this pilot study will also limit our ability to assess some clinical outcomes. However, we were still able to use this pilot study to determine the feasibility of this intervention.

### Conclusions

As the prevalence of CKD grows, primary care teams will increasingly be responsible for management of CKD. Clinical decision support tools may be a low-cost effective solution to enhance guideline-concordant care for this underdiagnosed disease. We describe the design and implementation of a pragmatic clustered randomized controlled trial to evaluate the feasibility and effectiveness an EHR-embedded electronic clinical decision support tool to improve management of CKD in primary care. Results from this study can guide design of future pragmatic eCDSS trials to improve CKD care.

## Abbreviations

ACEi: angiotensin converting enzyme inhibitor
ACR: urine albumin-creatinine ratio
ARB: angiotensin II receptor blocker
BP: blood pressure
BPA: best practice advisory
CKD: chronic kidney disease
eCDSS: electronic clinical decision support system trial arm
eCDSS+: electronic clinical decision support system and pharmacist follow-up trial arm
eGFR: estimated glomerular filtration rate
eGFR _Cr_: estimated glomerular filtration rate by serum creatinine
eGFR _Cys_: estimated glomerular filtration rate by serum cystatin-c
EHR: electronic health record
GEE: generalized estimating equation
ICD-10: International Classification of Diseases, Tenth Revision, Clinical Modification
KDIGO: Kidney Disease: Improving Global Outcomes
NP: nurse practitioner
NSAID: nonsteroidal anti-inflammatory drug
PCMH: primary care medical home
PCP: primary care provider

## Appendix

Multimedia Appendix 1 CONSORT‐EHEALTH checklist (V 1.6.1).
